## Results

The preparatory phase for the study is fulfilled. Recruitment started in June, 2015 and finished September, 2015. Results will be reported in 2016.

## Discussion

### Outcomes

The specific outcomes, such as primary outcome measures (The Trail Making Test, parts of the Wechsler Adult Intelligence Scale, 4th Edition, or WAIS-IV) were selected because they are widely used psychological tests [39,42]. They were thought to be sensitive to changes in the cognitive functions typically related to TBI. Moreover, these functions were assumed to be trained by the video games. The Trail Making Test is one of the most used neuropsychological tests globally, allowing comparisons to previous studies on TBI and rehabilitation. WAIS-IV tasks also are among the most used psychological tests in the world, and they are sensitive enough to discriminate even healthy adults. WAIS-IV has been standardized also in Finland - the home country of the participants - allowing us to compare our sample to national standards. The secondary outcome measures were selected so that a comprehensive picture of the potential changes in cognitive functions that can be assumed to be trained by the games (both the video games and the cognitive training game) is obtained. Moreover, we thought it is important to record changes in mood and self-efficacy as these influence daily life of a patient. Finally, for practical purposes it is important to gain knowledge of the feasibility of the games, as measured by adherence to the treatment and the participants’ personal experience with the game.

#### Primary Outcome

##### Processing Speed and Visuomotor Tasks

*The Trail Making Test (TMT)* requires visual search, scanning, speed of processing, mental flexibility, and executive functions [39]. The test consists of two parts. In the first part, patients are given a paper displaying circles numbered 1 to 5 in random order. The patient is told to draw lines that will connect the numbers in ascending order. In the second part, there are circles with numbers from 1 to 13 and letters from A to L. This time, the patient draws lines to connect the circles so that they alter between numbers and letters in an ascending order (for example: 1-A-2-B-3-C) and so on. The time it takes to complete the trail is measured in both parts of the test. Errors do not affect the final score, but they must be corrected by the patient [40,41].
*WAIS-IV tasks* (symbol search, coding and cancellation*)* are a test package used to measure cognitive skills of adult patients, especially skills of sorting out simple visual information, monitoring, making progress in the task, maintaining attention, visuomotor co-ordination and visual memory [42]. The tasks constitute 4 indices that measure different areas of cognitive skills. In symbol search and cancellation tasks, the participants perform a visual search in order to find out if a certain symbol is in the midst of other symbols. In the symbol search task, the symbols are organized in rows, and the participant has to indicate whether or not the required symbol was on each row. In the cancellation task, the participant looks for the same symbols during the whole task. In the coding task, the participant is given a set of numbers and symbols that match each other. Their task is to fill out an empty grid containing only numbers with the appropriate symbols matching those numbers. The test-retest reliabilities of the tasks used in this study ranged from 0.78 to 0.86 over an 8-82 day period in the original WAIS-IV standardization study [42]. A version of the test [42] containing norms for the Finnish population is used in this study.

#### Secondary Outcomes

##### Attention and Executive Functions

A *Simon task* [43,44] will be used to measure the inhibition component of executive functions [45]. This is a computerized visuomotor task in which correct responses and reaction times are measured. In the task, a blue or red square appears on either the left or right side of the screen. The participant is instructed to push the left button on a response pad each time a blue square appears and the right button each time a red square appears, irrespective of which side the square is presented. In congruent trials, the response button is on the same side as the square, and in incongruent trials the square is on the opposite side of the response button (ie, the irrelevant spatial information is conflicting with the correct response). The differences in reaction times and error rates between the incongruent and congruent trials (the Simon effect) are used as the dependent measurements in this task. These variables reflect the extra processing cost of having to inhibit the incompatible spatial location of the stimulus.

##### Working Memory

*WAIS-IV* (digit span) measures working memory [42]. In the first part of the task, the participants repeat numbers in the order they hear them. This task measures memory, coding, attention and auditory processing. In the second part, they repeat the numbers backwards. This task requires the use of working memory, processing information before giving an answer, internal processing and visuospatial organization. In the third part of the task, the participants repeat numbers in numerical order. This task again measures working memory and internal organization of the stimulus, but is more demanding than the other two tasks [42].
*The Paced Auditory Serial Addition Test* (PASAT) was originally developed by Gronwall [46] to measure auditory information processing speed, flexibility and calculation skills, in order to monitor the rehabilitation of patients with mild head injuries. This study includes a well-established version of the test in which the stimulus presentation rates were adapted for MS-patients by Rao and colleagues [47]. In the first part, single numbers are presented every 3 seconds. The patient adds each new number to the last number prior to it. In the second part, the numbers are presented every 2 seconds, but the task is the same. The test score is the number of correct sums given in each trial.

##### Depression

*The Patient Health Questionnaire* (PHQ-9) [48,49] includes 9 items where respondents are asked to indicate with four-point scale how often they have been bothered by any of the problems over the last two weeks (0 = not at all; 1 = several days; 2 = more than half of the days; 3 = nearly every day). Based on the individual items, a total score is formed: the higher the score, the more severe the depression symptoms (range 0-27).

##### Self-Efficacy

*The General Self-efficacy Scale* (GSC) [49] has been created to assess a general sense of perceived self-efficacy to predict coping with daily hassles as well as adaptation after experiencing a variety of stressful life events. The scale for 10 items is self-administered and responses are made on a 4-point scale (1 = Not at all true; 2 = Hardly true; 3 = Moderately true; 4 = Exactly true). It takes about 4 minutes to complete. The final composite score ranges from 10 to 40, and comprises the sum of all 10 responses: low scores represent a lower ability to cope with daily problems.

##### Executive Functions

The Behavior Rating Inventory of Executive Function-Adult Version (BRIEF-A) is a 75-item questionnaire that focuses on executive functions in daily life [50]. The questionnaire consists of a behavioral regulation index (inhibition, shifting, emotional control and self-monitoring) and a metacognition index (initiation, working memory, planning/organizing, task monitoring and of materials). The answers to this self-administered questionnaire are given in a three-point Likert scale format (never/sometimes/often). A global executive composite (GEC) will be formed by the total score. The test has been found to be reliable (an internal consistency of α .80-.94 for the clinical scales; α .96-.98 for the indexes) [50].

##### Feasibility

*Adherence:* Willingness to participate in the study (participation/refusal, yes, no); dropout for any reason (yes/no); involvement in the interventions for 8 weeks period (yes/no)
*Usability:* “Was the game usable?” (yes/no)
*Satisfaction:* “Have you been satisfied with the game?” (yes/no)
*Use:* “Would you like to use the game in the future?” (yes/no/maybe)

Background information including socio-demographic characteristics and illness history will be collected (age, gender, marital status, level of education, employment status, living situation, illness history, illness history, current digital game playing (hours a week). If needed, detailed information about each participant’s diagnosis and the time of traumatic brain injury will be collected based on electronic medical records to limit the amount of information to be collected from patients themselves.

#### Time for the Data Collection and Follow-Up

Patient data will be collected at three different times: at baseline, after the intervention (8 weeks), and as a follow-up, 3 months after the intervention. If required by the participant, he or she will receive a text message about 2 days before the meeting to remind them of the coming follow-up meeting.

#### Sample Size

The calculations for the sample size needed in each group are preliminary estimations to guide our data collection, which are based on previous studies: (1) TMT (version A) and (2) depression (PHQ-9). First, if a score on the TMT version will be about 71, the mean change in the scores during the follow-up will be 30, and standard deviation of the TMT scores will be 53 [41]. This difference between groups could be expected to be significant (with a power of 85%, *p*=.05) if the sample size in each group is 30 subjects. Second, if the average level of the PHQ-9 score is about 10, the mean change in the scores during the follow-up is then 3 (SD 5) [48]. The difference could be expected to be significant (with a power of 85%, *p*=.05) if the sample size in each group is 27 subjects. Thus, based on these preliminary power calculations, the sample size to be used in this study (30 in each group) is not very strong but will be reasonable for a feasibility study aiming to detect preliminary changes within the group, between baseline and follow-up outcome measurements. However, this means that the attrition rate of the study should be near 0%. The outcomes of this study will be used as a guide to estimate a sample size for a multi-center study to be conducted, hopefully in the future.

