#### Analysis Plan

All the participants will be analyzed at the baseline, after 8 weeks when the intervention has been finalized, and at 3 months, using all the scales for primary and secondary outcomes. Comparisons in possible differences between means in 3 intervention groups and 3 time points will be conducted using analysis of variance (ANOVA test). Possible post hoc tests may be performed using paired *t*-tests, or Chi square tests to detect significant differences before and after treatment in sub-groups, if needed. Further, significant differences between groups will be evaluated applying the unpaired Student’s *t*-test using the conventional 95% level of confidence. Statistical analyses will be done using SAS System for Windows, version 9.4 (SAS Institute Inc.). *P* values less than 0.05 will be considered statistically significant.

The cumulative monitoring data during the 8-week period regarding gaming for the total number of received parameters (frequency, timing, time) will be calculated. Feasibility information (secondary outcomes) available for each patient will be calculated (participation/refusal rate, measurement instrument filled, drop-outs, acceptability, usability, satisfaction, willingness) and compared to the highest possible representative numbers (100% participation rate; measurement instrument filled, drop-out rate 0%, acceptability 100%, usability 100%, satisfaction 100%, willingness to use games in the future 100%).

Criteria for feasibility are as follows:

Willingness to participate 80% (refusal rate 20%)We expect that more than 75% of the prescheduled measurements will be performed (adherence).Less than 25% of participants drop out for to any reason (adherence)The acceptability of the game use is at least 95% (in intervention and control groups) (adherence).Usability evaluation for the gaming system is at least 80% (1 item; dichotomous scale yes/no) (usability).More than 80% are satisfied with the games (1 item; dichotomous scale, yes/no) (satisfaction)We expect that 60% are willing to use the games later as part of their recovery process (use in the future).

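### The TMT-A sample size uses 53, described as the SD of scores, as if it were the SD of change; if it is the SD of scores, the 85% power rests on an unstated correlation of 0.5

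*Protocol article*

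**What the plan says.** The Sample Size section gives three inputs for the Trail Making Test part A (TMT-A): a starting level ("if a score on the TMT version will be about 71"), and then an effect and a spread ("the mean change in the scores during the follow-up will be 30, and standard deviation of the TMT scores will be 53"). It then concludes: "This difference between groups could be expected to be significant (with a power of 85" per cent, at p=.05 and 30 subjects per group. For the PHQ-9 it gives a mean change of 3, with an SD of 5 printed directly after the change, and arrives at 27 per group.

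The section then says that the chosen size serves to detect preliminary changes within a group between baseline and follow-up, and adds: "this means that the attrition rate of the study should be near 0" per cent. It calls the calculations preliminary.

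No baseline/follow-up correlation for the TMT appears anywhere in the article. The only retest figures are in the Primary Outcome section, under the WAIS-IV tasks: "The test-retest reliabilities of the tasks used in this study ranged from 0.78 to 0.86 over an 8-82 day period".

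**The concern.** The SD of a score on one occasion and the SD of a within-person change are different quantities. They are linked by the correlation between the two occasions, and they coincide only under a particular correlation. If an SD of scores is entered where the formula needs an SD of change, the resulting power depends on a correlation that nobody chose or justified.

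The stakes are the printed 85% power for a primary outcome, the statement that the sample size is reasonable, and the inference that almost no attrition can be tolerated. A reader who designs a later trial from this paragraph could also carry the confusion forward.

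**Working it through.** **Inputs.** Mean change 30, SD 53, power 85%, p=.05 and 30 per group, all from Sample Size. Sidedness is not stated, so two-sided is used. The PHQ-9 inputs (change 3, SD 5, n 27) serve as a cross-check. The TMT-A correlation r is not given, so it is an assumption and is varied.

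**Step 1: reproduce the printed figures.** Paired t-test, effect size = mean change / SD of change, noncentral t, two-sided 0.05.
- TMT-A: 30/53 = 0.566. The n for 85% power is 30.0, and power at n=30 is 85.0%.
- PHQ-9: 3/5 = 0.6. The n for 85% power is 26.9, printed as 27.

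Other readings of the TMT-A inputs do not give 30. A two-sample test with SD 53 needs 57 to 58 per group. A one-sided paired test needs 24. So 53 was entered as the SD of change.

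**Step 2: what this implies if 53 is the SD of scores.** With the same SD at both visits,

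SD of change = 53 × √(2(1 − r)).

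Setting this equal to 53 gives 2(1 − r) = 1, so r = 0.5.

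**Step 3: power over r.** Change of 30, two-sided 0.05, equal SDs. The between-group column is an unpaired t-test on change, with a difference of 30 between two arms.

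| r | SD of change | Within-group power, n=30 | n for 85% within-group | Between-group power, 30 per arm |
|---|---|---|---|---|
| 0 | 75.0 | 56% | 58 | 33% |
| 0.3 | 62.7 | 72% | 42 | 45% |
| 0.5 | 53.0 | 85% | 30 | 58% |
| 0.7 | 41.1 | 97% | 19 | 79% |
| 0.8 | 33.5 | 99.7% | 14 | 93% |

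Within-group power stays within 2 points of 85% for r from about 0.47 to 0.53. It is at least 85% for every r of 0.5 or more.

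**Step 4: dependence on equal SDs.** If times fall in proportion from a mean of 71 to 71 − 30 = 41, the follow-up SD becomes 53 × 41/71 = 30.6. Then SD of change = √(53² + 30.6² − 2r × 53 × 30.6), which equals 53 when r = 30.6/(2 × 53) = 0.29. Under that model, within-group power at n=30 is 81% at r=0.2, 85% at r=0.3 and 93% at r=0.5.

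**Step 5: attrition.** The Analysis Plan's feasibility criterion allows dropout of just under 25%. Losing 7 of 30 (23%) leaves 23 per group. With equal SDs, within-group power is then 59% at r=0.3, 74% at r=0.5 and 92% at r=0.7. How much attrition the calculation can bear therefore depends on the same unstated correlation.

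**The case against.** The strongest reply is that 53 may really be an SD of change, loosely described. The PHQ-9 sentence beside it attaches its SD to the change, and one formula reproduces both sample sizes. The source cited for the TMT values is not at hand, so this cannot be excluded. That stands. But in that case the sentence still misnames its input and needs correcting.

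A reader might infer that the printed power holds only at a correlation of exactly 0.5, or that the trial is underpowered. The article supports neither. From 0.5 upwards, 30 per group meets or exceeds 85% within-group power, and the 0.5 itself moves to about 0.29 if the SD shrinks in proportion to the mean.

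A reader might instead take the printed reliabilities of 0.78 to 0.86 as showing that power is ample. They belong to the WAIS-IV tasks over 8 to 82 days, not to the TMT, and the last visit is 3 months after an 8-week intervention. They do not supply the missing value.

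A third inference is that raw seconds are the wrong analysis scale. A mean of 71 with an SD of 53 does imply right skew: a normal model puts 9% of times below zero. The Analysis Plan says "Comparisons in possible differences between means in 3 intervention groups and 3 time points will be conducted using analysis of variance (ANOVA test") without fixing a scale, and a transformation is commonly left to an analysis plan. In simulation with skewed (lognormal) times at 30 per group, type I error stayed near 5%. The power gain from logs also depends on shape: for follow-up scores it was about 81% raw against 88% log under a lognormal distribution, but 78% raw against 68% log under a gamma. This shows no error in the article.

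Finally, the figures are labelled preliminary, the study is a feasibility trial, recruitment is reported as finished, and the PHQ-9 calculation stands separately. These points limit the consequence but do not make the description of 53 right.

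**Conclusion.** The description of 53 and its use do not match. The printed arithmetic is correct for an SD of change, while the text describes an SD of scores. If the text is literal and the SD is equal at both visits, the 85% rests on an unstated and unsupported correlation of 0.5. Over correlations from 0 to 0.7, within-group power at 30 runs from about 56% to 97%, so the direction of any error is unknown, and a shortfall arises only below 0.5.

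Any restated figure of this kind is within-group power only. The TMT-A sentence itself speaks of a difference between groups. For a between-group comparison of change, the same inputs give about 58% at a correlation of 0.5 and 79% at 0.7, and 85% needs a correlation of about 0.74. High paired power is therefore no ground for removing the attrition caution.

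**What to change.** In the Sample Size paragraph:

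1. State whether 53 is the SD of TMT-A scores or of the change in scores.
2. If it is of the change, correct the wording; the 30 and 85% then stand as within-group figures.
3. If it is of scores, state the assumed baseline/follow-up correlation and whether the SD is taken as equal at both visits. Replace the single 85% with power at 30 per group over a range of correlations, such as the table above.
4. Label the figure as within-group, and say that between-group power for change at 30 per group is lower.
5. Keep the attrition caution, but tie it to the restated figures.

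The cost is a few sentences. No extra patients, data or change of analysis are needed. The only drawback is that one round power figure becomes a range.

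### The 85% power stated for a TMT-A difference between groups is a within-group figure; on the same inputs the between-group power at 30 per arm is about 58%, and the paragraph's attrition condition conflicts with the feasibility criterion

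*Protocol article*

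**What the plan says.** The Sample Size section of the protocol article gives two calculations.

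- **TMT-A:** starting from a score of about 71, "the mean change in the scores during the follow-up will be 30" and "standard deviation of the TMT scores will be 53". The conclusion is "This difference between groups could be expected to be significant (with a power of 85" percent, at p=.05) "if the sample size in each group is 30 subjects".
- **PHQ-9:** from a level of about 10, a mean change of 3 (SD 5) has 85% power at p=.05 "if the sample size in each group is 27 subjects". This sentence speaks only of a difference and does not say between what.

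The paragraph then calls 30 per group not very strong but reasonable for a feasibility study "aiming to detect preliminary changes within the group, between baseline and follow-up outcome measurements". It adds that "this means that the attrition rate of the study should be near 0" percent.

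The Analysis Plan compares three groups at three time points by ANOVA. It evaluates differences between groups with the unpaired Student's t-test and treats p below 0.05 as significant. Among its feasibility criteria is "Less than 25% of participants drop out for to any reason (adherence").

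**The concern.** The TMT-A sentence attaches 85% to a contrast between arms, while the closing sentence describes change over time inside an arm. These contrasts have different standard errors. With equal SDs, the difference between two independent means has twice the variance of a single mean, so one sample size cannot give 85% power for both on the same inputs.

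The trial is a three-arm randomised comparison whose aim includes evaluating effects. A reader will take the between-group statement at face value and suppose that a true difference of that size would be missed about 15% of the time. If the figure belongs to the other contrast, a non-significant comparison between arms says less than it appears to.

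The attrition statements raise a second question: the trial could meet its own drop-out criterion while failing the condition on which its power figure rests.

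**Working it through.** **Inputs (Sample Size section).** TMT-A: difference 30, SD 53, n = 30 per group. PHQ-9: difference 3, SD 5, n = 27 per group. Significance level 0.05, power 85%. Two-sided testing is not stated; I assume it from the 95% confidence level in the Analysis Plan, and the reproduction below supports it.

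Standardised effects: TMT-A d = 30/53 = 0.566; PHQ-9 d = 3/5 = 0.60.

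**Step 1: reproduce the stated sizes.** One-sample (paired) t-test, noncentral t, df = n − 1, noncentrality = d√n.

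- TMT-A: 0.566 × √30 = 3.10, df 29, power 85.0%. Solving for 85% gives n = 30.00.
- PHQ-9: 0.60 × √27 = 3.12, df 26, power 85.1%. Solving gives n = 26.93, so 27.

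Both printed sizes are recovered exactly.

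**Step 2: try the alternatives.** Required n per group for 85% power:

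| Method | TMT-A | PHQ-9 |
|---|---|---|
| One-sample t, two-sided | 30.0 | 26.9 |
| One-sample normal approximation, two-sided | 28.0 | 24.9 |
| One-sample t, one-sided | 23.9 | 21.4 |
| Two-sample t, two-sided | 57.0 | 50.9 |
| Two-sample t, one-sided | 45.6 | 40.6 |

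No two-sample version comes near 30 or 27.

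**Step 3: between-group power on the same inputs.** Unpaired t-test, df = 2n − 2, noncentrality = d√(n/2), taking 30 (or 3) as the between-arm difference and 53 (or 5) as the SD of the compared quantity.

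- TMT-A, n = 30: 0.566 × √15 = 2.19, df 58, power 57.8%.
- PHQ-9, n = 30: 0.60 × √15 = 2.32, df 58, power 62.8%.
- PHQ-9, n = 27: 0.60 × √13.5 = 2.20, df 52, power 58.1%.

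**Step 4: drop-out inside the feasibility criterion.** 23 of 30 retained is a loss of 7/30 = 23.3%, which is below 25%. (22 retained would be 26.7%, beyond it.)

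- TMT-A between groups: 0.566 × √11.5 = 1.92, df 44, power 46.7%.
- TMT-A within a group: 0.566 × √23 = 2.71, df 22, power 73.7%.
- PHQ-9 between groups: 0.60 × √11.5 = 2.03, df 44, power 51.2%.

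**Step 5: what the SD refers to.** The text gives 53 as the SD of TMT scores, whereas a paired test needs the SD of the change. If scores have the same SD at both times and correlation r, the SD of change is 53 × √(2(1 − r)), which equals 53 only at r = 0.5. The document gives no such correlation for TMT. As an assumed range at 30 per group, r = 0.5 to 0.7:

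- unpaired t-test on change scores: 58% to 79%;
- baseline-adjusted comparison, residual SD 53 × √(1 − r²): 70% to 86%.

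For PHQ-9 the SD is printed directly after the mean change and may already be the SD of change.

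**The case against.** The strongest reply is that the paragraph largely discloses its scope. It calls the calculations preliminary, admits the size is not very strong, and names within-group change as the target; for that target, on the stated inputs, 85% is numerically right. This stands as an account of where the figure came from. It does not make the TMT-A sentence true, because that sentence says between groups.

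Four further inferences are tempting, and the document does not support them.

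- **That both outcomes carry the false label.** Only the TMT-A sentence says between groups. The PHQ-9 sentence follows directly on a change over follow-up and can be read as within-group.
- **That the true miss rate is 42%.** That is 100 − 58, and it depends on 53 being the SD of whatever is compared and on a change over follow-up serving as the between-arm difference. Step 5 shows how far power moves if 53 is the SD of scores and the analysis uses baseline. The calculation in the document states no correlation or adjustment, so the higher figures cannot be credited to it either.
- **That the 85% will be carried into the multi-centre trial.** The section says the later sample size will be guided by this study's outcomes, not by this power figure.
- **That the plan adopts 25% attrition for power.** The 25% is a success threshold for feasibility, while the near-zero figure is a warning about what the power needs. They serve different purposes, but nothing in the text says how both are meant to hold.

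It can also be said that the unpaired t-test follows an ANOVA over groups and time points. This does not restore 85%. A simple one-way ANOVA at a single time point, three arms of 30, gives about 60% for TMT-A if one arm differs by 30 from the other two, and 47% if the arms are evenly spaced over 30. The repeated-measures version would need correlations that the document does not give.

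**Conclusion.** The point holds. The TMT-A statement of 85% power for a between-group difference is wrong as written. The sizes 30 and 27 are one-sample or paired t-test sizes, and the paragraph contradicts itself on which contrast it describes. That diagnosis is firm, since both sizes match exactly and no two-sample calculation comes close.

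The replacement figures are conditional. With the document's effects taken as between-arm differences, its SDs taken as those of the compared quantity, and two-sided 0.05, between-group power at 30 per group is about 58% for TMT-A and 63% for PHQ-9. At 23 per group it is about 47% and 51%. Reaching 85% between groups would take about 58 and 51 per group before drop-out.

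The objection to using an SD of scores for an SD of change is clear for TMT only. The attrition statements are in tension: drop-out just inside the feasibility criterion takes even the within-group TMT-A power to about 74%.

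**What to change.** Rewrite the Sample Size paragraph, without enrolling more participants:

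1. Remove the between-groups wording from the TMT-A sentence. Say that the 85% refers, for both outcomes, to change within one group by a paired t-test, two-sided 0.05.
2. Say that for TMT this treats 53, given as the SD of scores, as the SD of change. Say for PHQ-9 which SD the 5 is.
3. Add the between-group power by the unpaired t-test: about 58% (TMT-A) and 63% (PHQ-9) at 30 per group, about 47% and 51% at 23 per group. State the assumption that the quoted SDs are those of the compared quantity.
4. Reconcile the two attrition statements, for example by saying that the below-25% criterion judges feasibility only, and giving the power that remains at that level of loss.
5. If baseline-adjusted power is shown at all, present it as conditional on an assumed correlation and mark it as such; neither that analysis nor a TMT correlation is in the document.

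The cost is one paragraph and a less favourable stated power. Recruitment is already reported as finished, and neither conduct nor analysis changes.
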